# SPRAYDYE: a phase I/II randomised pilot study to assess the safety and feasibility of topically applied AKRO-6qcICG, a cathepsin-activatable fluorescent imaging agent, for real-time intraoperative resection margin assessment in breast-conserving surgery

**DOI:** 10.3389/fsurg.2026.1845151

**Published:** 2026-07-22

**Keywords:** breast imaging <radiology & imaging, breast surgery <surgery, clinical pharmacology, clinical protocols, surgical pathology <pathology

## Abstract

**Introduction:**

The incidence of tumour-positive surgical resection margins (TPRMs) after breast-conserving surgery (BCS) remains high, ranging from 10 to 40%. A TPRM, defined as breast cancer cells at the edge of the resected specimen at pathological evaluation, implies residual tumour and necessitates re-resection or boost radiation. To prevent these additional treatments, intraoperative near-infrared (NIR) fluorescence imaging with the topically applied, fluorescently quenched, cathepsin-activatable imaging agent AKRO-6qcICG might be used to detect residual cancer in the surgical cavity and guide additional resection during BCS. Cathepsins are proteolytic enzymes that are upregulated by breast cancer (associated) cells and therefore are suitable targets for tumour imaging. *Ex vivo* validation studies have shown that topically applied AKRO-6qcICG allows for clear breast cancer visualization and the detection of TPRMs. The proposed phase I/II study in healthy volunteers and breast cancer patients will assess the local and systemic safety of a single, topical dose of AKRO-6qcICG and its feasibility for intraoperative margin assessment during BCS.

**Methods and analysis:**

A total of six healthy volunteers (Part A) and 16 breast cancer patients (Part B) will be enrolled. In Part A, AKRO-6qcICG will be topically applied randomly on drawn blisters in two doses as will the vehicle compound, and one blister will be untreated functioning as a negative control. Physician and subject will remain blinded. In Part B, a single dose of AKRO-6qcICG will be topically applied in the surgical cavity. The primary objective is, with the occurrence of treatment-emergent (serious) adverse events as primary outcome measure. Secondary outcome measures include local and systemic tolerability parameters such as wound healing, numeric rating scales of pain and pruritus, vital signs, electrocardiogram parameters, clinical laboratory tests and pharmacokinetic parameters. Among the exploratory outcome measures are the diagnostic accuracy of the imaging agent to detect residual tumour in the surgical cavity and the tumour-to-background ratio of the fluorescent signal.

**Ethics and dissemination:**

This protocol has been approved by the Medical Ethical Committee Leiden-Den Haag- Delft (METC- LDD). The protocol is registered at EU Clinical Trials Register number 2025-523166-24-00. The results of this study will be reported through peer- reviewed publications and conference presentations.

**Clinical Trial Registration:**

https://ctis.eu/trial/2025-523166-24-00?from=search

## Article summary

### Strengths and limitations of this study

Safety is thoroughly assessed in both healthy volunteers and breast cancer patients.Incomplete surgical resection is a major complication with huge impact on patient's life.A clinically relevant endpoint will be used as the primary endpoint.Absence of positive tumour margins will impact the exploratory outcome of this trial.Systemic exposure will not be comparable between healthy volunteers and patients.

## Introduction

Breast cancer is the most commonly diagnosed malignancy and the leading cause of cancer-related death among women worldwide (1). For most patients with newly diagnosed breast cancer, curative treatment consists of breast-conserving surgery (BCS) followed by adjuvant radiotherapy (2, 3). Although BCS provides survival outcomes comparable to those of total mastectomy, it is associated with a 10%–40% risk of positive resection margins, which increase the likelihood of local recurrence and frequently necessitate re-excision surgery or boost radiotherapy (4–10). Oncoplastic breast-conserving surgery has been shown to reduce re-excision rates, but approximately 10.5% of patients still require further surgery (11). These additional interventions are also associated with increased morbidity, poorer cosmetic outcomes, a higher risk of complications, increased healthcare costs and adverse psychological effects (12). Various pathological and imaging techniques have been investigated to improve intraoperative margin assessment and reduce positive resection margin rates following BCS; however, most have significant clinical and technical limitations that have hindered their widespread adoption (13). Current intraoperative margin assessment strategies include frozen section analysis, imprint cytology, specimen radiography and intraoperative ultrasound (13). Although frozen section analysis can reduce re-excision rates, its routine implementation is limited by increased operative time, specialised pathology expertise, tissue sampling error and variable diagnostic performance across institutions. Frozen section analysis has been reported to achieve pooled sensitivity and specificity of approximately 81% and 97%, respectively, although substantial heterogeneity between studies has been observed (*I*^2^ = 90.8%) (14). An ideal method for margin assessment during BCS would swiftly, non-invasively, and in real-time detect residual malignancy on the surgical cavity surface, ideally being cost-effective and user-friendly. Intraoperative tumour-targeted near-infrared (NIR) fluorescence imaging is a promising method that could meet these criteria. This technique can highlight tumour tissue by administrating a fluorescent contrast agent that selectively binds to or is activated by tumour cells. A special NIR fluorescence (700–900 nm) camera system is used to detect the contrast agent (15).

Currently, most tumour-targeted contrast agents for fluorescence-guided BCS are administered intravenously prior to surgery (16, 17). Alternatively, contrast agents could be topically applied to the surgical cavity after tumour resection, offering fast visualization of residual tumour, smoother integration into the surgical workflow, lower chances of systemic side effects, and improved cost-effectiveness. Several topical fluorescent probes have been tested *in vivo* in a preclinical setting and *ex vivo* on resected human breast cancer specimens, but these agents were not able to adequately distinguish malignant from benign breast tissue (18, 19). A promising topically applied contrast agent for fluorescence-guided BCS is AKRO-6qcICG, a fluorescently quenched, protease-activatable probe composed of indocyanine-green (ICG) and a NIR quencher conjugated to a peptide Cbz-Phe-Lys core (20). It functions as a “smart” probe, producing a fluorescent signal only when processed by tumour-associated enzymes – cathepsin B, L, and S - which are highly upregulated in breast cancer compared to healthy tissue (21, 22). AKRO-6qcICG leverages a latent lysosomotropic effect (LLE), accumulating fluorescent fragments in lysosomes, enhancing signal strength and duration (20). In an *ex vivo* validation study AKRO-6qcICG, formulated in a thermosensitive gel, effectively differentiated between human breast cancer and adjacent healthy tissue and allowed for the detection of tumour-positive resection margins with a high sensitivity and considerable specificity (23, 24). However, due to the soft, pliable nature of a resected breast cancer specimen, its geometry does no longer accurately correspond to that of the resection cavity. Consequently, correlating an *ex vivo* detected tumour-positive resection margin to the *in vivo* location of the residual tumour that needs to be excised can be very difficult. Combining the *ex vivo* margin assessment with the *in vivo* detection of residual tumour tissue on the surgical cavity walls seems to be the most promising approach. Therefore, we propose the SPRAYDYE-study: ‘*Fa**S**t intrao**P**erative **R**esection margin **A**ssessment in breast-conserving surgery using a topicall**Y** applie**D**, fluorescentl**Y**-quenched, protease-activatable imaging ag**E**nt’.*

## Methods and analysis

### Objectives

The proposed first-in-human phase I/II study aims to evaluate the local and systemic safety of administering a single topical dose of AKRO-6qcICG in both healthy volunteers and breast cancer patients. Additionally, it will examine the feasibility of using this approach for intraoperative margin assessment during breast-conserving surgery.

### Hypothesis

It is hypothesized that a single topical dose of AKRO-6qcICG is safe and can be used to detect residual breast cancer in the surgical cavity during BCS.

### Study design

The study consists of two parts, Part A and B. Part A of the study is a phase I, single dose, double-blind, randomized, vehicle-controlled, single-centre study in healthy volunteers (Figure 1). A total of six healthy volunteers will be included. The healthy volunteers will be evaluated for the local and systemic safety and tolerability of a single topical dose AKRO-6qcICG in thermosensitive gel vs. thermosensitive gel alone on wounded skin. In order to derisk any potential adverse events (AEs) of the compound and formulation in a patient setting, we are using the suction blister model in humans. This is routinely performed and enables systematic evaluation of local tolerability and safety signals quickly and robustly (25). Part B is a monocentre, single-dose, open-label, single arm, exploratory (proof-of-concept) phase II study in 16 breast cancer patients undergoing BCS that will evaluate the safety and feasibility of a single topical dose of AKRO-6qcICG for the detection of residual tumour in the surgical cavity.

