### Sample size

Six healthy volunteers and 16 breast cancer patients will be enrolled. As this is an exploratory study, the sample size is not based on formal statistical considerations. The proposed sample size will be sufficient to test the hypothesis.

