### Study drug

AKRO-6qcICG, the sterile lyophilized Drug Product and the sterile 19.5% w/v Poloxamer-407 thermosensitive gel were manufactured in the department of Clinical Pharmacy and Toxicology, Leiden University Medical Center, according to cGMP. The study drug consists of AKRO-6qcICG Drug Product, reconstituted on the day of use in DMSO and diluted in in the thermosensitive poloxamer gel, with a final concentration of 3.5% DMSO in the study drug gel. AKRO-6qcICG is a small organic molecule whose structure is composed of both a NIR dye indocyanine green (ICG) and a non-fluorescent quencher moiety (IRDye QC-1) covalently bound to a dipeptide scaffold. 6qc-ICG is a fluorescently quenched, cathepsin-activatable imaging agent. The vehicle gel part of the study drug is composed of 19.5% w/v Poloxamer 407 solution in water for injections. Poloxamer 407 is a triblock copolymer containing a central hydrophobic polyoxypropylene block flanked by a hydrophilic polyoxyethylene (PEG) block at either end. Such poloxamers have the general formula O(C2H4O)x(C3H6O)y(C2H4O)zH. At low temperatures the polymer strands are highly solubilized by extensive hydrogen bonding to water molecules and the solution is relatively free flowing. At higher temperatures the hydrophobic fragments (polyoxypropylene blocks) aggregate to a much higher degree, leading to the exclusion of water molecules and subsequent spherical micelle formation. This results in gelation of the solution, which is reversible as the temperature decreases and the polymer strands are once again solubilized by hydrogen bonding with water molecules. The gel transition temperature is dependent on the poloxamer concentration. The concentration of 19.5% w/v Poloxamer-407 was based upon measurements of representative surgical breast cavity surface temperature during regular procedures by way of a hand-held IR temperature measurement gun (21, 22). 6qc-ICG is stable in the presence of acids, bases and metal ions.

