### Intervention

Part A will include one day for screening, one treatment period of approximately 8 h and two blister evaluation visits, three and 12 days post-dosing. To mimic a surgical wound, four circular application areas of approximately 2 cm in diameter (corresponding to the wound area of approximately 1 cm in diameter and approximately 0.5–1 cm in diameter of the surrounding area) will be made on the skin of the forearm of a healthy volunteer using a blister suction device (NP-4, Electric Diversities, Maryland, USA). By using negative pressure, the device induces a 10 mm diameter painless blister in approximately 60–90 min. The roof of the formed blister is pierced with a needle and the blister fluid is aspirated. Then the blister roof, i.e., epidermal sheet, will be harvested. The four areas will be denoted as ‘Area 1’, ‘Area 2’, ‘Area 3’, ‘Area 4’. Treatments will be applied directly to the blister wounds and the surrounding skin. The four treatment conditions (AKRO-6qcICG 50 µM = 0.115 mg/l, AKRO-6qcICG 25 µM = 0.0575 mg/l, vehicle (placebo), untreated) will be randomized by computer to the four treatment areas. Both the investigator and the healthy volunteer will be blinded through sealed syringes. The assigned treatment will be applied directly onto approximately 1 cm of wounded skin and approximately 0.5–1 cm in diameter of the surrounding area. A minimum of 5 cm distance will be achieved between wounded skin. Pharmacokinetic (PK) blood and urine sample collection, local and systemic tolerability assessment, clinical wound assessment, and clinical (NIR) imaging will be performed on the study day and during the two follow-up visits.

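### As described, the Part A placebo gel is not matched to the active gel for DMSO, so a local reaction in excess of vehicle could not be attributed to AKRO-6qcICG rather than to its solvent

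*Protocol article*

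**What the plan says.** Study design labels Part A "double-blind, randomized, vehicle-controlled, single-centre study in healthy volunteers" and describes the comparison as "AKRO-6qcICG in thermosensitive gel vs. thermosensitive gel alone on wounded skin". The stated purpose of the blister model is given there as "In order to derisk any potential adverse events (AEs) of the compound and formulation in a patient setting".

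Study drug says that the active product is "reconstituted on the day of use in DMSO" and then diluted in the poloxamer gel, "with a final concentration of 3.5% DMSO in the study drug gel". The same section adds: "The vehicle gel part of the study drug is composed of 19.5% w/v Poloxamer 407 solution in water for injections". DMSO is not listed in that sentence.

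Intervention randomises four conditions to the four forearm areas of each volunteer: the 50 µM gel, the 25 µM gel and, as controls, "vehicle (placebo), untreated". It gives no composition for the placebo. The abstract mentions a vehicle compound, also without composition.

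**The concern.** A vehicle control should contain everything in the active product except the agent. For this product that means gel and DMSO. The comparator is described as gel alone, and the only composition given for the vehicle gel has no DMSO. Read that way, active and placebo sites differ in two components, and the label vehicle-controlled promises more than the comparison delivers.

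Pain, pruritus and wound healing at the application site are named secondary outcomes, and they are the ones exposed to the mismatch. Part A is also the only part with a randomised control, since Part B is open-label and single-arm. If a local reaction appears at the active blisters, Part A is where one would learn whether the agent or the solvent caused it. A mismatch in composition cannot be repaired in the analysis once dosing is done.

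**Working it through.** The article has no planned figure to reproduce: Sample size says that "the sample size is not based on formal statistical considerations", and the point depends on no power or error rate. The check is a comparison of what each site receives.

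**Inputs.** Six volunteers, four areas each (Study design, Intervention). Final DMSO 3.5% in the study drug gel; vehicle gel 19.5% w/v Poloxamer 407 in water for injections (Study drug). The 3.5% is given once, without distinguishing the 25 and 50 µM gels.

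**Content of each condition, as the text reads.**

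| Condition | Sites | Gel | DMSO | Agent |
|---|---|---|---|---|
| 50 µM | 6 | yes | 3.5% | yes |
| 25 µM | 6 | yes | 3.5% if the single figure covers both strengths | yes |
| Vehicle | 6 | yes | none listed | no |
| Untreated | 6 | no | 0% | no |

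Sites with DMSO: 6 × 2 = 12 active. Placebo sites with DMSO, as described: 0 of 6.

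**What each contrast estimates.** Write G for the effect of the gel, D for that of 3.5% DMSO, and A50 and A25 for those of the agent at each strength, added together for simplicity.

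- Vehicle − untreated = G
- 50 µM − vehicle = A50 + D
- 25 µM − vehicle = A25 + D
- 50 µM − 25 µM = A50 − A25
- 50 µM − untreated = G + D + A50, the complete formulation

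Four condition means give three independent contrasts, and there are four unknowns (G, D, A50, A25). A50 and A25 each appear only together with D. The difference A50 − A25 can be estimated, but it concerns only the step from 25 to 50 µM. Adding volunteers sharpens each contrast without separating A from D.

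**With DMSO matched in the placebo.** The difference in DMSO between active and vehicle becomes 3.5% − 3.5% = 0 percentage points. Then 50 µM − vehicle = A50, 25 µM − vehicle = A25, and vehicle − untreated = G + D. Three contrasts now identify three quantities: A50, A25 and the full vehicle effect.

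**Sensitivity to how the 25 µM gel is made (assumption).** If it were made from a half-strength DMSO stock, its DMSO would stay at 3.5% and the dose contrast would be balanced. If it were made by diluting the 50 µM gel 1:1 with plain gel, its DMSO would be 3.5% / 2 = 1.75%. DMSO would then run 0, 1.75 and 3.5% across placebo, low and high strength, and no contrast would isolate the agent. The single figure in the article fits the first case more plainly.

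**The case against.** The strongest reply is that the article never gives the composition of the placebo syringe. The sentence on the vehicle gel describes the gel component of the active product before the reconstituted drug is added. The phrase in Study design leaves DMSO out on both sides, although the active side certainly contains it, so gel alone may simply mean gel without the agent. The full protocol or pharmacy documents may specify a matched vehicle. This stands as a limit: the absence of DMSO from the placebo is an inference. It does not remove the point, because the article goes into composition in some detail, calls the comparator gel alone, and nowhere puts DMSO in it.

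Several stronger readings are tempting, and the documents do not support them:

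- *Active versus vehicle is the only randomised contrast.* It is not. Four conditions are randomised within each volunteer, so active versus untreated and 50 versus 25 µM are randomised as well.
- *Part A cannot meet its derisking aim.* The active sites carry agent, gel and DMSO together and are compared with untreated sites, so the complete formulation is still tested.
- *The primary outcome or the condition for Part B is undermined.* Treatment-emergent events are to be listed, and Part B depends on the 50 µM gel being well tolerated in Part A. Neither requires agent and solvent to be told apart.
- *The dose contrast is confounded too.* That needs unequal DMSO in the two gels, which the article does not state.

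**Conclusion.** The point holds in limited form. As described, the control is not a matched vehicle. If the placebo is prepared that way, an excess local reaction at active over vehicle sites cannot be attributed to AKRO-6qcICG rather than to DMSO. Within that contrast the overlap is complete: 12 of 12 active sites carry DMSO and 0 of 6 placebo sites do.

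The consequence is one of interpretation, not of error rates or sample size, and it bites only if a local reaction is seen; if the active sites are quiet, little is lost. The conclusion rests on reading gel alone and the vehicle gel description literally. If the placebo already contains 3.5% DMSO, what remains is a correction to the text. Either way, the composition should be settled before the first volunteer is dosed.

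**What to change.** Reconcile Study design, Study drug and Intervention by stating the composition of the placebo. Define it as the same poloxamer gel with the same final DMSO fraction as the active gels, prepared by the same dilution step. Confirm in the text that this fraction is equal in the 25 and 50 µM gels, so that the dose contrast is balanced as well.

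If the placebo is to stay DMSO-free, drop the label vehicle-controlled and report active-minus-placebo differences as the effect of agent plus DMSO.

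The cost is one preparation step in the pharmacy and an edit to the product description. The downside is small: the placebo site is also exposed to DMSO, and vehicle versus untreated then measures gel and DMSO together rather than gel alone.

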**Figure 1 F1:**
[figure not shown]
Schedule of assessments Part A..

### Setting

Part A of this study will take place at the Centre for Human Drug Research (CHDR), Leiden, The Netherlands. Part B of the study will take place in the Leiden University Medical Center (LUMC), Leiden, The Netherlands.

### Participants

For Part A, healthy volunteers, recruited through advertising, will be screened for eligibility at the CHDR screening unit. For Part B, all patients scheduled for breast-conserving surgery at the LUMC will be screened for eligibility during multidisciplinary team meetings and, when eligible for participation, informed about the study by their attending physician or specialized breast cancer nurse. Written informed consent will be obtained by investigators or dedicated staff before any study related procedure will be performed. The fundamental concepts outlined in the Declaration of Helsinki will be followed during the execution of the trial.

### Sample size

Six healthy volunteers and 16 breast cancer patients will be enrolled. As this is an exploratory study, the sample size is not based on formal statistical considerations. The proposed sample size will be sufficient to test the hypothesis.

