### Statistical analysis

Descriptive statistics will be depicted as mean (standard deviation, sd) or median (interquartile range, IQR). All statistical tests will be performed two-sided. A *p*-value of less than 0.05 will indicate a statistically significant difference. For part A and B, analysis of the safety and tolerability endpoints ((TE)(S)AEs, vital signs, ECG, and clinical laboratory tests) will be conducted with SAS 9.4 for Windows or newer (SAS Institute Inc., Cary, NC, USA). All (TE)(S)AEs will be listed and safety variable values outside the reference range will be flagged. Analysis of the pharmacokinetic endpoints (AUC_inf_, AUC_last_, CL/F, C_max_, t_1/2_, t_lag_, t_max_, Vz/F, Ae_last_, Ae_%_, CL/R) in plasma and urine will be conducted with R 3.6.1 for Windows or newer (R Foundation for Statistical Computing/R Development Core Team, Vienna, Austria, 2019). The individual PK parameters will be summarized per treatment group and, if applicable, will be presented graphically as boxplots. For Part B, the most recent version of SPSS (IBM, Armonk, New York, USA) will be used for statistical analysis of the exploratory NIR fluorescence imaging endpoints. Diagnostic accuracy analysis (including sensitivity, specificity, positive predictive value, and negative predictive value) will be performed based on a per resection wall (*in vivo* images)/per resection plane (*ex vivo* images) basis. To investigate differences in MFI between tumour tissue and adjacent healthy breast tissue on the surgical cavity walls and on the resection planes, the Wilcoxon signed-rank test will be used. The Spearman's correlation coefficient will be determined to investigate the correlation between the TBR of a fluorescent hotspot on a resection plane and the margin width at that location.

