## Expected limitations and difficulties

Creating a representative, large surgical wound in a healthy volunteer is unethical. Instead, in Part A, four blisters will be induced on healthy volunteers, which will have a smaller total surface area compared to the surgical wound in Part B. Consequently, the total dose of AKRO-6qcICG applied to the healthy volunteers will be lower than the total dose breast cancer patients will receive in Part B. As a result, the unwanted systemic exposure measured in Part A may not fully represent that in Part B. However, using the blister model does allow for the assessment of local safety and tolerability as well as acute systemic toxicity. Additionally, it can be questioned if a detectable systemic concentration of the study drug will be achieved at all: due to the intended single-dose and topical application of the investigational product, the systemic exposure in patients in Part B is considered to be very low, especially when taking into account that the vast majority of the topically applied AKRO-6qcICG will be washed off and suctioned away after 10 min of incubation time.

The exploratory objectives of the proposed SPRAYDYE-trial - assessment of the feasibility of using AKRO-6qcICG for intraoperative margin assessment during breast-conserving surgery - may present challenges. First of all, accurate assessment of the diagnostic accuracy requires imaging sufficient surgical cavity walls containing residual tumour. To enhance the likelihood of imaging residual tumour, patients with a high risk of tumour-positive margins will be enrolled in Part B. Still, with only 16 patients enrolled, there is a possibility that none will have residual tumour, thereby preventing the calculation of sensitivity and positive predictive value. Additionally, capturing perpendicular NIR fluorescence images of all cavity walls of a breast-conserving surgery wound could pose a challenge due to the narrow space. This could be partly overcome by using a laparoscopic camera head instead of an open system.

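### The article says 6 and 16 participants suffice to test safety and tumour detection, though neither is tested, and wrongly says PPV cannot be calculated if no residual tumour is found

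*Protocol article*

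**What the plan says.** The Sample size section fixes the numbers ("Six healthy volunteers and 16 breast cancer patients will be enrolled") and disclaims a formal basis: "As this is an exploratory study, the sample size is not based on formal statistical considerations". The next sentence reads: "The proposed sample size will be sufficient to test the hypothesis". The only hypothesis in the article is in the Hypothesis section, that "a single topical dose of AKRO-6qcICG is safe and can be used to detect residual breast cancer".

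Statistical analysis sets general rules ("All statistical tests will be performed two-sided"; "A *p*-value of less than 0.05 will indicate a statistically significant difference"). For safety it lists the events and flags out-of-range values. For imaging it plans sensitivity, specificity, PPV and NPV per cavity wall and per resection plane. It also plans a Wilcoxon signed-rank test on fluorescence intensity and a Spearman correlation with margin width.

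Expected limitations and difficulties says that, with 16 patients, "there is a possibility that none will have residual tumour, thereby preventing the calculation of sensitivity and positive predictive value".

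**The concern.** Two statements about what the trial can deliver do not fit the rest of the article.

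First, sufficiency to test a hypothesis presupposes a test: a null value, a threshold or a success rule, and a size that makes the answer informative. The article supplies none of these for safety or for detection, and it accepts that the condition to be detected may not occur at all.

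Second, the limitations section treats PPV as lost together with sensitivity when there is no residual tumour. The denominators differ. Sensitivity divides by walls with tumour, PPV by walls that fluoresce, and the second group does not vanish because the first does.

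At stake is what the trial may claim. A reader could take the first statement as a warrant for confirmatory language, and the second as a reason to leave out a figure that exists.

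**Working it through.** There is no power or precision figure in the article to reproduce. The check is what 6 and 16 can show.

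**Inputs.** n = 6 and n = 16 (Sample size). Two-sided 5% level (Statistical analysis). Positive-margin rate 10–40% (Introduction). Four-way classification of walls (Exploratory outcomes). Five cavity walls per patient (Intervention).

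**Safety.** If none of n participants has a given event, the exact two-sided 95% upper limit is 1 − 0.025^(1/n):
- n = 6: 1 − 0.025^(1/6) = 45.9%
- n = 16: 1 − 0.025^(1/16) = 20.6%

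The chance that an event with true rate 10% is never seen is 0.9^n:
- n = 6: 0.9^6 = 53.1%
- n = 16: 0.9^16 = 18.5%

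These figures are for one specified kind of event. For any adverse event after surgery, zero is an unlikely count.

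**Detection.** Assume that the margin rate p applies per patient and equals the rate of residual tumour in the cavity. The article does not say this. Expected positive patients are 16p, and the chance of none is (1 − p)^16:

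| p | Expected positives | Chance of none |
|---|---|---|
| 10% | 1.6 | 18.5% |
| 20% | 3.2 | 2.8% |
| 30% | 4.8 | 0.3% |
| 40% | 6.4 | 0.03% |

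With m positive units, taken as independent and all detected, the exact 95% lower limit for sensitivity is 0.025^(1/m). For 3/3 it is 29.2%, and for 6/6 it is 54.1%.

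The named tests do not fill the gap. The Wilcoxon test concerns contrast between tumour and healthy tissue, and the Spearman coefficient concerns margin width. Neither carries a criterion for detection. Moreover, with one cavity pair per patient, the smallest two-sided signed-rank p-value is 2 × 0.5^m. That is 0.0625 for m = 5 and 0.031 for m = 6, so significance needs at least six positive patients. The chance of fewer than six is 99.7% at p = 10% and 32.9% at p = 40%.

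**PPV with no residual tumour.** By the article's own categories, a wall that lights up without tumour is a false positive (FP). With no tumour anywhere, TP = FN = 0. Then:
- Sensitivity = TP/(TP + FN) = 0/0, undefined.
- PPV = TP/(TP + FP) = 0/FP = 0 if FP ≥ 1. It is 0/0 only if no wall fluoresces.
- Specificity = TN/(TN + FP), still defined.

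Illustration with assumed counts: 16 × 5 = 80 walls, 8 of them fluorescent, none with tumour. PPV = 0/8 = 0 and specificity = 72/80 = 90%. If the 8 walls were independent, the exact upper limit for PPV would be 1 − 0.025^(1/8) = 36.9%. Several may come from one patient, so that limit should not be used as it stands.

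**The case against.** The strongest reply is that both faults are of wording. The study calls itself exploratory, events are listed descriptively, and accuracy is only an exploratory outcome. No decision rule depends on the sufficiency sentence. Having no formal basis and being sufficient are not strictly contradictory; the second is merely unsupported. The risk of having no positive margins is disclosed. The size itself is ordinary for a first-in-human study. All of this stands, and the objection here is to the claim, not to the numbers enrolled. It does not rescue the sentence, which follows directly on the disclaimer and asserts adequacy for a test that does not exist.

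The 18.5% chance of no residual tumour also uses the bottom of a range quoted for breast-conserving surgery in general. Part B is meant to enrol patients at raised risk of positive margins, so the true chance is probably nearer the low end of the table. That stands too. Even at 40%, the limits on sensitivity remain wide.

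Three stronger readings may tempt a reader, and the documents support none of them:
- **That an unfavourable result would be hidden.** The limitations paragraph is commentary, not an analysis rule. Every wall is to be classified, and specificity and PPV are planned without exception, so false positives would still show.
- **That PPV of 0 would be the worst finding possible.** At zero prevalence, any agent that fluoresces at all has PPV 0 by construction. The primary outcome is safety, where a serious event would weigh more.
- **That a clean result would be written up as confirmation.** This predicts conduct, and nothing in the text says so.

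How adverse-event incidence will be tabulated, and with what intervals, may properly be left to the full protocol or SAP and is not criticised here.

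**Conclusion.** The point holds as two incorrect statements. It is not a fault in the design.

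The claim of sufficiency is unsupported for both halves of the hypothesis. On safety, a clean record for a given event is compatible with true rates up to 45.9% in Part A and 20.6% in Part B. On detection, the article itself allows for having nothing to detect. The size of that risk rests on the assumption that the general margin rate carries over per patient to residual cavity tumour.

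The PPV statement is wrong as a general statement and needs no assumption beyond the article's own definitions. It is right only when no wall fluoresces, which is not the condition the article names. A PPV of 0 in a sample without tumour says little about performance, but it can be calculated and should be reported.

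No planned analysis changes. The correction is still worth making because it settles what the trial may say it has shown.

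**What to change.** 1. **Sample size.** Replace the sufficiency sentence with what the size delivers. For example: safety and detection will be described, not tested; if no participant has a given event, the exact two-sided 95% upper limit for its rate is 45.9% with 6 participants and 20.6% with 16. If an expected number of tumour-positive patients is added, give 1.6 to 6.4 and state the assumption behind it.
2. **Expected limitations and difficulties.** Limit the statement on what cannot be calculated to sensitivity. Add that PPV is undefined only if no wall fluoresces.
3. **Reporting.** State that PPV will be given as true positives over all fluorescent walls, including a value of 0, beside the false-positive count and specificity. Any interval should allow for several walls per patient. Add a note that PPV of 0 at zero prevalence says little about the agent.

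The cost is a few sentences and slightly less favourable wording. Enrolment, procedures and planned analyses are unaffected.
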